##### Acceptability, appropriateness, and feasibility

Adolescents who participate in *Hoosier Sport Re-Social* will rate the feasibility, acceptability, and appropriateness of the intervention using the FIM, AIM, and IAM, respectively (each described in Aim 2).

##### Compliance

Screen time compliance will be assessed for each of the two physical activity data collections by determining the weekly average social media usage.

*Cost.* The cost of the intervention will be monitored throughout the study period and determined in comparison to the prospective study budget.

#### Aim 3: sample size calculation

A target sample size of 50 participants has been selected based on prior recruitment rates from the Hoosier Sport program, which has consistently engaged approximately 60 students per semester and achieved 100% retention over the past two semesters. This sample size will allow us to estimate feasibility indicators such as recruitment, retention, and intervention fidelity with reasonable precision. For example, a sample size of 50 would allow us to estimate a retention rate of 85% with a 95% confidence interval of ± 10%. This level of precision is appropriate for assessing progression criteria to a larger trial. Additionally, although not powered to detect statistical significance, this sample will support estimation of effect sizes related to body satisfaction, social media literacy, and psychosocial outcomes, which will inform future trial design and sample size calculations.

#### Aim 3: data analysis

##### Quantitative analysis of survey measures

In our analysis process, we will begin by reviewing the completeness and distributions of all variables. If any variables demonstrate non-normal distributions, we will apply normalizing transformations as required. Internal consistencies of scaled scores will be evaluated using Cronbach’s alpha to ensure reliability.

This study’s primary objective is to evaluate the intervention’s feasibility using the following indicators: Feasibility of Intervention Measure (FIM), Acceptability of Intervention Measure (AIM), Intervention Appropriateness Measure (IAM), attendance, and retention. Descriptive statistics—including means, standard deviations, and proportions—will be used to summarize these outcomes. A priori thresholds for success will be defined as a mean score of ≥ 16 out of 20 on the FIM, AIM, and IAM, representing a “good” rating. Attendance and retention rates will also be reported as proportions, with retention thresholds aligned with a minimum of 85% as an acceptable benchmark.

Secondary outcomes (e.g., body satisfaction and social media literacy) and exploratory outcomes (e.g., body appreciation and physical literacy) will be analyzed by assessing changes from pre- to post-intervention using paired-sample *t*-tests. Repeated measures ANOVAs will be used to further examine time effects and potential interactions. Age and BMI will be included as covariates in these models to enhance interpretation of between- and within-group differences.

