## Methods/design

### Overview

This study is structured into three distinct phases to address body image perceptions and develop interventions for adolescent females enrolled in under-resourced rural middle and high schools (grades 6–9). The first phase, AIM 1, involves conducting a comprehensive needs assessment through community-engaged research to build foundational knowledge about body image, social media usage, and physical activity levels among rural adolescents. This phase aims to identify current physical activity levels and assess facilitators and barriers to positive body image within the adolescents’ context.

In the second phase, AIM 2, the focus shifts to co-designing the Hoosier Sport Re-Social intervention with key community stakeholders. This involves collaborating with adolescents, parents, and teachers to develop a prototype multi-level intervention and implementation protocol. Participant involvement is central to the Hoosier Sport Re-Social protocol. Adolescents, parents, and teachers are not only research participants but also co-creators of the intervention. Through a series of structured co-design sessions, these stakeholders actively contribute to identifying problems, generating solutions, and refining the final prototype, ensuring the program is contextually relevant and responsive to community needs. The goal is to create an intervention that is responsive to the needs and preferences of adolescents, specifically targeting the promotion of a positive body image.

The third phase, AIM 3, involves piloting the Hoosier Sport Re-Social intervention with a sample of 50 adolescents, divided into 25 in the intervention group and 25 in the control group. This phase will evaluate the feasibility and acceptability of the intervention, assessing both trial-related and intervention-specific feasibility indicators. Feasibility refers to the extent to which an intervention can be successfully delivered in a specific setting, considering factors such as recruitment, retention, acceptability, adherence, and implementation fidelity. The overarching hypothesis of the study is that the successful completion of these three phases will result in a feasible and effective intervention protocol for promoting a positive body image among adolescent females in rural settings. Figure 2 provides a timeline of these aims.

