Our hypotheses for Aim 3 include several expectations: achieving full enrollment *(N* = 50), retaining 85% of participants by the intervention’s end, maintaining a 75% attendance rate, obtaining a mean score of ≥ 16 (considered a “good” score) on the Feasibility of Intervention Measure (FIM), AIM, and IAM, and ensuring an 80% fidelity rate in adhering to intervention procedures. Our selection of implementation measures (AIM, FIM, IAM) aligns with core constructs from the Theoretical Framework of Acceptability (TFA) and maps onto RE-AIM dimensions (e.g., implementation and acceptability). This approach supports a structured evaluation of the intervention’s feasibility and future scalability. The Hoosier Sport Re-Social intervention is described in accordance with the Template for Intervention Description and Replication (TIDieR) framework to enhance reproducibility. A structured fidelity checklist has also been developed to monitor delivery, adherence, and adaptations across implementation sessions, ensuring consistency with the intended intervention protocol. Progression to a full-scale randomized controlled trial (RCT) will be considered if the pilot study demonstrates the following: enrollment reaches at least 80% of the target sample (*N* = 50); retention at post-intervention assessment is 85% or higher; session attendance averages 75% or above; fidelity to the intervention protocol is maintained at or above 80% based on fidelity monitoring; and participants report mean scores of at least 16 out of 20 on validated measures of feasibility (FIM), acceptability (AIM), and appropriateness (IAM). These criteria align with recommendations for determining readiness to advance from a pilot to a full-scale trial in behavioral intervention research.

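### Aim 3 names a paired pre-post t-test first, which does not use the planned control group as comparator, and designates no between-group estimate as the effect size for the future trial

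*Protocol article*

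**What the plan says.** The Overview of the protocol article describes Aim 3 as a pilot in a "sample of 50 adolescents, divided into 25 in the intervention group and 25 in the control group". It does not say how the two groups are formed.

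Under Aim 3: data analysis (Quantitative analysis of survey measures), the secondary and exploratory outcomes "will be analyzed by assessing changes from pre- to post-intervention using paired-sample" *t*-tests. The text does not say whether the test covers all 50 participants or the intervention arm only. Two further sentences follow: "Repeated measures ANOVAs will be used to further examine time effects and potential interactions", and "Age and BMI will be included as covariates in these models to enhance interpretation of between- and within-group differences".

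Aim 3: sample size calculation says that "this sample will support estimation of effect sizes related to body satisfaction, social media literacy, and psychosocial outcomes". It adds that these estimates are meant to guide how the later trial is planned and sized. What that trial would be is stated under Aim 3: design: "Progression to a full-scale randomized controlled trial (RCT) will be considered" if the feasibility thresholds are met.

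**The concern.** An RCT is sized on a difference between arms. A paired pre-post test estimates a change over time in whichever participants enter it. The article therefore names, first and most explicitly, a test that cannot deliver the quantity its sample size section wants. It does not designate the analysis that could deliver it: group is not named as a factor, the interactions are not specified, and no between-group estimate is identified as the planning effect size.

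A team following the text could carry the paired change into the sample size of the next trial. That trial could then be far too large or too small, depending on which participants were tested and on how scores drift over the programme for reasons unrelated to it.

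**Working it through.** **The plan's own figure.** The only Aim 3 precision figure is that "a sample size of 50 would allow us to estimate a retention rate of 85% with a 95% confidence interval of ± 10" percentage points. Wald half-width: 1.96 × √(0.85 × 0.15 / 50) = 0.099, or 9.9 points. It reproduces. It concerns retention and says nothing about the precision of an effect size.

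**Inputs.** From the article: 25 per group, outcomes measured before and after. Assumed, because the article gives none: true group effect *d*, time trend *t* common to both arms, both in SD units of the score, and pre-post correlation *r* = 0.7.

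**What each analysis estimates.**
- Paired change, arms pooled: ½(*d* + *t*) + ½*t* = *d*/2 + *t*
- Paired change, intervention arm only: *d* + *t*
- Group-by-time contrast (difference in change): (*d* + *t*) − *t* = *d*

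**Consequence for the next trial.** With two-sided alpha 0.05 and power 80%, n per arm = 2(1.960 + 0.842)²/δ² ≈ 15.70/δ², rounded up.

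| *d* | *t* | Pooled: δ, n per arm | Treated only: δ, n per arm | Between-group: δ, n per arm |
|---|---|---|---|---|
| 0.5 | 0 | 0.25, 252 | 0.50, 63 | 0.50, 63 |
| 0.5 | +0.2 | 0.45, 78 | 0.70, 33 | 0.50, 63 |
| 0.5 | −0.2 | 0.05, 6280 | 0.30, 175 | 0.50, 63 |
| 0.3 | 0 | 0.15, 698 | 0.30, 175 | 0.30, 175 |
| 0.3 | +0.2 | 0.35, 129 | 0.50, 63 | 0.30, 175 |

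With no drift, pooling halves the effect and so quadruples the sample size (252/63 = 4), while the treated-only change is unbiased. With drift, both paired readings are off.

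**Simulation check** (20,000 runs, 25 per group, *r* = 0.7). For *d* = 0.5 and *t* = 0, the mean estimates were 0.25 (pooled), 0.50 (treated only) and 0.50 (between-group). For *d* = 0.5 and *t* = +0.2, they were 0.45, 0.70 and 0.50. With no intervention effect and *t* = +0.2, the paired test was significant in 44% of runs (pooled, n = 50) and 23% (treated only, n = 25), against 5.0% for the between-group contrast.

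**Precision at *r* = 0.7, in SD units.**
- Pooled paired change: √(2 × 0.3 / 50) = 0.11
- Treated-only paired change: √(2 × 0.3 / 25) = 0.15
- Difference in change: √(2 × 0.3) × √(2/25) = 0.22
- Baseline-adjusted ANCOVA: √(1 − 0.7²) × √(2/25) = 0.20

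**The case against.** The strongest reply is that the paired test is not the whole plan. With two groups and two time points, group-by-time is the natural candidate among the unspecified interactions, and the covariate sentence speaks of between-group as well as within-group differences. The sample size section never says that the planning effect sizes will come from the paired tests, and the article never calls those tests primary. Naming an interaction term is also the kind of detail often left to an analysis plan.

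Much of this stands. A reader might infer that the control data are thrown away, or that every planned effect size is biased. The text supports neither, since a group contrast may well be intended. Three further inferences also fail:
- **Baseline is missing from the ANOVA.** In a repeated measures ANOVA the baseline score is already one of the responses.
- **Regression to the mean will inflate the change.** Aim 3 uses convenience sampling with no body-image threshold for entry, so the article gives no selection on extreme scores.
- **Sex must be an Aim 3 covariate because Table 1 adjusts for it.** Table 1 lists the Aim 1 cross-sectional regressions and does not bind Aim 3.

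What the reply does not remove is that the article does more than leave a detail open. It states a specific uncontrolled test for these outcomes and gives the ANOVA only a supplementary role. It also states a use for the effect sizes that the named test cannot serve.

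**Conclusion.** The point holds in a limited form. The first-named analysis does not use the control group as a comparator, and no between-group estimate is designated as the effect size for the future RCT. If the paired change were used for that purpose, it would estimate *d*/2 + *t* or *d* + *t* instead of *d*. Under the illustrative assumption of *d* = 0.5, that means 252 per arm (pooled, no drift) or 33 per arm (treated only, drift +0.2 SD) where 63 is right.

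These sizes rest on assumed values of *d* and *t*, and the simulation and standard errors also on *r*. The direction and size of the error change with the drift, and the treated-only reading without drift carries none.

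This is a should-fix. The outcomes are secondary or exploratory in a feasibility pilot that claims no power for them. The progression criteria rest on enrolment, retention, attendance, fidelity and the FIM, AIM and IAM scores, so none of them is affected.

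**What to change.** In the Aim 3 quantitative analysis section:

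1. For each secondary and exploratory outcome, make the intervention-minus-control difference, with a 95% CI and a standardised size, the reported effect size.
2. Obtain it from the group-by-time contrast or from an ANCOVA adjusted for the baseline score, and say in advance which. If the groups are not comparable at baseline, the two can estimate different quantities.
3. Limit paired pre-post changes to description within each arm.
4. Label the contrast as non-randomised if the groups are not formed at random.
5. In the sample size section, say that this difference and its interval are what will inform the next trial.

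The change is to wording only, since the pre and post measurements are already planned. The cost is a wider interval: a standard error of about 0.20 to 0.22 SD at the assumed *r* = 0.7 (95% half-width about 0.40 to 0.43 SD), against 0.11 to 0.15 SD for the paired change. That width is the real uncertainty about the between-group effect with 25 per arm, and the next trial's planners need to see it.

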**Methods:**

This study follows the Standard Protocol Items: Recommendations for Interventional Trials (SPIRIT) guidelines and is structured around three aims. First, we will conduct a cross-sectional study with adolescent girls in grades 6 through 9 to examine the relationship between body satisfaction, physical activity levels, and social media use. Second, we will develop the Hoosier Sport Re-Social intervention using a co-design process that actively involves adolescents, parents, and school staff to ensure relevance and feasibility. Finally, we will conduct a mixed-methods pilot study in two rural middle and high schools to assess feasibility and acceptability. The intervention will be implemented within physical education and health classes over a 6-week period. Primary outcomes will include feasibility indicators such as recruitment, retention, fidelity, and participant engagement. Secondary outcomes will include measures of body satisfaction and social media literacy, while exploratory outcomes will examine changes in psychosocial factors and physical literacy.

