### Aim 3: To establish proof-of-concept and test Hoosier Sport Re-Social's feasibility, acceptability, and appropriateness

#### Aim 3: design

The third phase of the study will evaluate the feasibility of the Hoosier Sport Re-Social intervention (#NCT06556719) with 6th through 9th grade students from a rural middle or high school, conducted twice weekly over an 8-week period (ORBIT Phase Ib). Our assessment will focus on recommended feasibility measures for feasibility studies [28]. Alongside these measures, we will explore outcomes including self-reported weekly moderate-to-vigorous physical activity (MVPA) and physical literacy, body satisfaction, daily social media use duration, various psychosocial factors (such as self-esteem, body appreciation), and psychological needs using the BPNSFS.

Following the initial feasibility test, we will refine and retest the *Hoosier Sport Re-Social* intervention during the subsequent semester. To support intervention delivery, college student mentors—enrolled in upper division undergraduate or graduate public health programs—will collaborate with our research team. These mentors will undergo a 4-week training course before working with the middle or high school students. Their participation in delivering the intervention will be part of their academic coursework, earning them credit hours. The intervention is delivered by trained college students enrolled in upper-division public health and kinesiology courses. This model supports sustainability and scalability by leveraging an existing service-learning partnership between the university and the rural school. It also enhances relatability, as adolescents may feel more comfortable engaging with near-peer facilitators.

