#### Aim 3: setting and sample

For the pilot study, we aim to recruit a total of *N* = 50 6th through 9th grade students. Similar to Aim 2, we will employ convenience sampling, striving for diversity in terms of biological sex and physical activity involvement. Our goal is to enroll an approximate 50% female and 50% male participant ratio, encompassing both regular and non-regular physical activity participants.

To be eligible for participation, students must meet specific criteria: currently enrolled in 6th through 9th grade at the school, possess parental consent to participate, provide their agreement to study participation (assent), commit to attending all school days during the intervention period, and be available for both baseline and post-intervention data collection. These criteria are crucial for the study’s integrity and aim to ensure comprehensive data collection and participation continuity.

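### The programme is delivered within PE and health classes, but the Aim 3 outcome tests treat children as independent, so any within-class correlation makes the pre-post p-values too small and the intervals too narrow

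*Protocol article*

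**What the plan says.** Delivery: the abstract's Methods say "The intervention will be implemented within physical education and health classes over a 6-week period". The Aim 3 design section adds that trained college students deliver the programme.

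Allocation: the Overview says the 50 adolescents are "divided into 25 in the intervention group and 25 in the control group". Neither the unit nor the method of allocation is given. The Aim 3 setting and sample section says "we will employ convenience sampling, striving for diversity in terms of biological sex and physical activity involvement", and enrolment is by individual parental consent and child assent.

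Schools: the abstract says "we will conduct a mixed-methods pilot study in two rural middle and high schools to assess feasibility and acceptability". The Aim 3 design section describes the study as "with 6th through 9th grade students from a rural middle or high school, conducted twice weekly over an 8-week period", which reads as one school.

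Analysis: the quantitative analysis section assigns paired t-tests to pre-post change in the secondary and exploratory outcomes and then states "Repeated measures ANOVAs will be used to further examine time effects and potential interactions". Age and BMI are the only covariates. The article mentions no class, school or mentor term, no ICC, no cluster-robust error and no design effect. Feasibility indicators are summarised descriptively.

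Later use: the Aim 3 sample size section says the pilot is not powered for significance. It will support effect-size estimates, "which will inform future trial design and sample size calculations".

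**The concern.** Children taught in the same class share sessions, a room, a teacher and probably the mentors. If one class goes unusually well or badly, many children move together. The paired t-test counts each of them as a separate piece of evidence, so its standard error is too small whenever the within-class ICC of change is above zero. The repeated measures ANOVA, as described, has the same feature for its time effect and, under some allocations, for its group-by-time term.

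This is a method the article names, not a detail it leaves open. At stake are the p-values and intervals for body satisfaction, social media literacy, body appreciation and physical literacy, and how much confidence a planner of the next trial would place in them.

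**Working it through.** **The plan's own precision figure.** The only precision stated for Aim 3 is ±10% for a retention rate of 85% with 50 children. The usual formula gives 1.96 × √(0.85 × 0.15 / 50) = 0.099, so it reproduces, for 50 independent children.

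**Inputs.** From the article: 25 children per group, delivery within classes, and the named tests. Not in the article, so assumed: ICC of change from 0.01 to 0.10, and one, two or four equal classes among the 25 treated children (m = 25, 12.5 or 6.25 per class).

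**Pre-post test in the treated group.** The true variance of the mean change exceeds the variance the test assumes by about DE = 1 + (m − 1) × ICC. The real two-sided error of a nominal 5% test is about 2 × [1 − Φ(1.96/√DE)].

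| ICC | Classes | DE | Real error | Interval should be wider by √DE |
|---|---|---|---|---|
| 0.01 | 1 | 1 + 24 × 0.01 = 1.24 | 7.8% | 1.11 |
| 0.01 | 2 | 1 + 11.5 × 0.01 = 1.115 | 6.3% | 1.06 |
| 0.05 | 1 | 1 + 24 × 0.05 = 2.20 | 18.6% | 1.48 |
| 0.05 | 2 | 1 + 11.5 × 0.05 = 1.575 | 11.8% | 1.25 |
| 0.05 | 4 | 1 + 5.25 × 0.05 = 1.26 | 8.1% | 1.12 |
| 0.10 | 1 | 1 + 24 × 0.10 = 3.40 | 28.8% | 1.84 |
| 0.10 | 2 | 1 + 11.5 × 0.10 = 2.15 | 18.1% | 1.47 |

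Simulation of 20,000 null trials with a t-test on change scores agrees: 18.6%, 11.5% and 8.0% at ICC 0.05 with one, two and four classes.

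**Group-by-time test.** With two visits and two groups, and before covariates, this equals a two-sample t-test on change. The result depends on how classes relate to arms.

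- *Classes nested in arms, both arms clustered.* The variance ratio is DE, as above. Simulated at ICC 0.05: 19.8%, 12.3% and 8.1% with one, two and four classes per arm.
- *Only the treated arm clustered.* The ratio is (DE + 1)/2. At ICC 0.05 this is (2.20 + 1)/2 = 1.60 with one class, giving 12.1%, and (1.575 + 1)/2 = 1.29 with two, giving 8.4%. Simulated: 11.9%, 8.4% and, with four classes, 6.3%.
- *Both arms mixed in the same classes and sharing the same class effect.* The class effect cancels in the comparison. Simulated: 4.3% to 5.3% across ICC 0.01 to 0.10, so no inflation. In the same runs the treated-arm pre-post test still rejected in 5.6% to 18%.

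The pre-post result therefore holds under any allocation. The between-arm result does not.

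**The case against.** The strongest reply is that no stated decision turns on these tests. The feasibility analysis is descriptive, and every progression criterion is a threshold on enrolment, retention, attendance, fidelity or mean scores on the three implementation measures. The outcome tests are secondary or exploratory in a pilot declared not powered for significance. This stands, and it keeps the severity low. It does not make the named tests valid, because low power does not excuse a false-positive rate above the nominal level.

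The size also rests on assumed values. Individually enrolled children from four grades could be spread over more, smaller classes, where the inflation is smaller: about 8% with four classes at ICC 0.05. This also stands, and is why a range is given.

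A reader might infer three stronger things that the article does not support:

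- *That intact classes are enrolled or treated as units.* The text says delivery is within classes, while students are a convenience sample with individual consent.
- *That the between-arm test is certainly inflated.* This depends on the unstated allocation unit, and the inflation vanishes if both arms share the same class effects.
- *That the next trial will be too small.* The article says only that effect sizes will inform its planning. Nothing excludes a design effect, and ignoring clustering mainly distorts standard errors rather than the effect sizes carried forward.

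**Conclusion.** The point holds in limited form. The article combines class-based delivery with child-level tests and no allowance for class. If the within-class ICC of change is above zero, the pre-post p-values are too small and the intervals too narrow. In the treated group the real error of a nominal 5% test is roughly 6-8% at ICC 0.01, 12-19% at 0.05 and 18-30% at 0.10 with one or two classes. The ICC and class counts are assumptions.

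For the group-by-time test the article does not settle whether there is inflation, because it leaves the allocation unit and class count unstated and gives two versions of the number of schools. The consequences are confined to secondary and exploratory results and their use in planning. Severity is low.

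**What to change.** In the Aim 3 quantitative analysis section:

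- State the allocation unit and the number of classes, and reconcile the number of schools between the abstract and the Aim 3 design section.
- Report secondary and exploratory outcomes as estimates with 95% intervals that allow for class. If there are enough classes, use a mixed model with a random class effect and small-sample degrees of freedom.
- If there are too few classes (for example one or two per arm), give no p-values. Inflate the variance by 1 + (m − 1) × ICC, that is, widen the interval by its square root, over a stated ICC range such as 0.01 to 0.10, labelled as an assumption.
- Include a school term only if school does not coincide with arm, since otherwise the two cannot be separated.

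In the Aim 3 sample size section, add that effect sizes carried to a class-delivered full trial will be combined with a design effect over a range of ICCs, because this pilot cannot estimate the ICC reliably. For scale, classes of 25 give a design effect of 1.24 at ICC 0.01 and 2.20 at 0.05.

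The cost is a change of wording plus a record of each child's class and school, including controls. The downside is wider intervals and fewer p-values on outcomes the plan already describes as not powered.

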MET	CAPL-2, Sex	To examine the effect of physical literacy (CAPL-2) and sex on physical activity levels (MET).
BSQ	CAPL-2, Sex	To determine the relationship between physical literacy and body image, adjusting for sex.
BAS-2	CAPL-2, Sex	To explore how physical literacy influences body appreciation, accounting for sex.

All models will use linear regression. For each model, we will report unstandardized beta coefficients, standard errors, 95% confidence intervals, and p-values. Variables will be checked for assumptions of linearity, normality, and multicollinearity prior to analysis

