**Fig. 5 Fig5:**
[figure not shown]
Intervention- and trial-related outcomes

Additionally, preliminary behavior outcomes will be measured through replicating the measures of AIM 1 (BSQ, BAS-2, CAPL-2, pedometer wear, and a youth survey). These combined measures will provide data on potential changes from pre- to post-intervention in body satisfaction, body appreciation, physical literacy and activity levels, and social media usage.

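### The Aim 3 outcome models adjust for age and BMI but name no sex term or sex-specific estimate, although about half the sample is to be male and the programme is meant for girls

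*Protocol article*

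**What the plan says.** Under Aim 3: data analysis (Quantitative analysis of survey measures), the Protocol article lists "Secondary outcomes (e.g., body satisfaction and social media literacy) and exploratory outcomes (e.g., body appreciation and physical literacy" and says that they "will be analyzed by assessing changes from pre- to post-intervention using paired-sample" t-tests. It continues: "Repeated measures ANOVAs will be used to further examine time effects and potential interactions". The covariate sentence follows: "Age and BMI will be included as covariates in these models to enhance interpretation of between- and within-group differences". Sex is not mentioned. Nor does the text say whether age and BMI enter as main effects or crossed with time, whether they are centred, or whether BMI is measured once or twice.

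Four other places bear on this:

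- **Groups.** The Overview plans "a sample of 50 adolescents, divided into 25 in the intervention group and 25 in the control group".
- **Sex mix.** Aim 3: setting and sample says: "Our goal is to enroll an approximate 50% female and 50% male participant ratio".
- **Target.** The Abstract describes a programme designed for girls, and the primary objective in the Background concerns body satisfaction among adolescent females.
- **Use of the results.** Aim 3: sample size calculation says that the pilot is not powered for significance, but that its effect sizes will inform the design and sample size of a later trial.

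In Aim 1, all ten regressions in Table 1 include sex. These include four models of the BSQ and three of the BAS-2, one of them described as "To explore how physical literacy influences body appreciation, accounting for sex". Aim 3 measures the BSQ and BAS-2 again.

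**The concern.** There are two linked problems with the stated covariate set.

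First, the reason given for it does not follow from the methods named. One of the two methods has no place for covariates. In the other, entered in the simplest way, they cannot affect change within a child. Age and BMI may therefore be listed as adjustment while the pre-post results stay exactly as they were.

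Second, and more important, the set leaves out the variable that separates the target population from the rest of the sample. Followed as written, the analysis gives one average change, or one group difference in change, over girls and boys together. If the programme works differently in the two sexes, that average describes neither of them. It is also the figure that would be carried into the planning of the next trial.

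**Working it through.** The plan states no figure on this point, so there is none to reproduce. The check is algebra, confirmed on simulated data, followed by an illustration of dilution.

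**1. Covariates and within-child change.** There are two occasions, pre (t = 0) and post (t = 1). With g for group and u for the child effect, the repeated measures model with main-effect covariates is

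y = a + b·t + c·g + d·t·g + e·age + f·BMI + u + error.

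Subtracting pre from post gives change = b + d·g + error. Baseline age and BMI cancel, so b (time) and d (group-by-time) cannot move.

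This was confirmed on one simulated data set of 25 + 25 children. Assumptions not in the documents: age uniform from 11 to 15.5 years, BMI mean 21 and SD 4, within-child error SD 5, true change +2 in control and +5 in intervention.

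| Model | Time effect, groups pooled (SE) | Group-by-time (SE) | Between-subject group term |
|---|---|---|---|
| No covariates | 2.953 (1.046) | 4.304 (2.021) | 1.28 |
| + age, BMI as main effects | 2.953 (1.046) | 4.304 (2.021) | 1.00 |
| + age, BMI, sex as main effects | 2.953 (1.046) | 4.304 (2.021) | 1.12 |

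The paired t-test gives the same mean change, 2.953 (SE 1.046). Only the between-subject group term moves, and that term is not change.

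**2. Covariates crossed with time.** The model is now change = b + d·g + h·age + k·BMI + error. Over 4,000 simulated trials:

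- Centred, without the group term: time effect 3.53 with SE 1.02, the same as unadjusted.
- Uncentred, without the group term: b is the change at age 0 and BMI 0. Its SE rises from 1.02 to 12.0, and the rejection rate falls from 93% to 6.5%.
- Group-by-time is unbiased (3.02 adjusted, 3.01 unadjusted). Adjustment moves it by 0.30 on average in a single trial (SE 2.03 against 1.99).

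Age and BMI can therefore adjust the group difference in change, but only if they are crossed with time or, equivalently, entered in a model of change.

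**3. What a sex term does.** Step 1 shows that sex as a plain additive covariate also leaves change untouched. In a second simulation girls gained 6 from the intervention and boys 0 (assumed). The group effect on change was 2.99 both without sex and with additive sex. Only a group-by-sex term recovered about 0 for boys (0.03) and 6 for girls (5.96).

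**4. Consequence for planning (illustrative).** With half girls and half boys, the pooled effect is 0.5 × girls' effect + 0.5 × boys' effect. For 80% power at two-sided 5% (assumed), n per arm ≈ 2 × (1.96 + 0.84)² / d² = 15.68 / d². Take 0.4 SD in girls (assumed):

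| Boys' effect (assumed) | Pooled effect | n per arm from pooled effect | n per arm from girls' effect |
|---|---|---|---|
| 0.4 SD | 0.4 SD | 15.68 / 0.16 = 98 | 98 |
| 0.2 SD | 0.3 SD | 15.68 / 0.09 = 174 | 98 |
| 0 | 0.2 SD | 15.68 / 0.04 = 392 | 98 |

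With the t-distribution in place of the normal, the last row becomes 394 and 100. If the effect does not differ by sex, pooling does no harm.

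**5. Precision in girls.** 25 per arm × 0.5 = 12.5 girls per arm. Without baseline adjustment the SE of a group difference is √(1/12.5 + 1/12.5) = 0.40 SD, so the 95% CI is about ±0.78 SD. For the whole sample it is √(2/25) = 0.28 SD, about ±0.55 SD.

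**The case against.** The strongest reply is that the article does not say how age and BMI enter, and that such coding is normally left to a full analysis plan. That stands. A reader might infer that the adjusted results must be either identical to the unadjusted ones or meaningless. The documents do not support this: centred covariate-by-time terms leave the time effect undistorted and validly adjust group-by-time. The uncentred case is conjecture about software, and even there group-by-time stays unbiased and the paired t-test still gives an intact estimate of change. The covariate sentence also refers to between-group differences, where age and BMI do act. If BMI were re-measured and entered as time-varying, the cancellation would not apply to it.

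On sex, a reader might infer that adding it to the covariate list would mend the pre-post comparison. It would not (step 3). Table 1 is limited support: its models are cross-sectional, enter sex additively, and share only the BSQ and BAS-2 with the outcomes named for Aim 3. Social media literacy is absent from the table, and CAPL-2 appears only as a predictor. The prose model 1 for the BSQ in Aim 1 also omits sex. The unspecified interactions in the ANOVA sentence do not rule sex out. Nor do the progression criteria restrict the later trial to girls. Whether Aim 3 should enrol boys at all is a separate question that a covariate list cannot settle.

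What the reply does not remove is that the article does fix a covariate set and gives a reason for it. The set lacks sex, and no sex-specific estimate is promised for a programme aimed at girls and tested in a mixed sample.

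**Conclusion.** The point holds in limited form. The stated benefit of age and BMI for within-group differences does not arise in the paired t-test, or from baseline main effects in the repeated measures model. It needs centred terms crossed with time, which the article does not specify. That part is algebra and rests only on two occasions and covariates fixed at baseline.

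The more important part is the missing sex-specific estimate. The analysis as described yields a mixed-sex effect size for planning, while the stated objective concerns girls. The size of the harm is unknown, because the documents give no effect by sex. It ranges from none, if the effect is equal in both sexes, to about a fourfold error in sample size (394 against 100 per arm) if it is 0.4 SD in girls and absent in boys. These outcomes are secondary or exploratory in an unpowered pilot, so the weight is modest, and the feasibility thresholds and progression criteria are not touched.

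**What to change.** For each secondary and exploratory outcome, name one model for the between-group difference in change: regress the post score on baseline score, group, sex, group-by-sex, and mean-centred baseline age and BMI. With the baseline score in the model, the group estimates are the same whether the outcome is the post score or the change. Report the estimate in girls alongside the overall estimate at the observed sex mix, each with a 95% CI and described as exploratory. State that age and BMI are baseline values. Use this model in place of the repeated measures ANOVA with covariates. The paired t-tests can stay as unadjusted description.

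The cost is a change of wording, using variables the article already names. Sex and group-by-sex take two degrees of freedom. The girls' estimate will be imprecise: at 12 to 13 per arm, about ±0.8 SD before any gain from baseline adjustment. It should therefore be read together with the overall estimate when the next trial is sized, and not alone.
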